### 9.3.3 Secondary endpoints

#### i. feasibility outcomes:

- The proportion of patients randomised to the intervention group who are able to maintain HDT15 during the entire MT procedure will be calculated with their 95% confidence interval.
- The hospital admission-to-arterial access time (i.e. time to arterial puncture) will be described by median, first and third quartiles (Q1 and Q3) for each group.

#### ii. safety outcomes:

- Mean values of systolic blood pressure, diastolic blood pressure and oxygen saturation at entry in the Emergency Room, at entry in the angio suite and every 15 minutes from the start to the end of MT; they will be treated as continuous variables and calculated as mean with their 95% confidence interval for each group.
- Proportion of patients presenting one or more episodes of vomiting from randomisation to the completion of MT will be calculated with their 95% confidence interval for each group.
- Reasons for HDT15 discontinuation (e.g., intolerable discomfort, observed severe discomfort in non-communicative patients, vomiting, neurological worsening,

headache, or respiratory distress), minor adverse events, and MT-related technical challenges will be recorded and reported as proportions with 95% confidence intervals.

- The proportions of patients who had an increase of  $\geq 4$  points on the NIHSS score within  $24 \pm 12$  hours of the randomisation will be calculated with their 95% confidence interval for each group.
- The proportions of patients who had SICH within  $24 \pm 12$  hours will be calculated with their 95% confidence interval for each group.
- The proportions of patients with pneumonia within the first 72 hours after randomisation will be calculated with their 95% confidence interval for each group.
- Safety data, including serious and non-serious adverse events, as well as reasons for HDT15 discontinuation (e.g. discomfort, vomiting, neurological worsening, headache, respiratory distress) and technical challenges related to MT will be reported for both treatment arms. Adverse events will be categorized according to the Medical Dictionary for Regulatory Activities (MedDRA) v28.0.

iii. **efficacy** outcomes:

- functional outcome at 3 months, assessed with the ordinal score on the modified Rankin scale (shift across outcomes on the mRS between groups).
- Percent change in NIHSS ( $[(\text{Admission NIHSS} - \text{time-point NIHSS}) \times 100 / \text{Admission NIHSS}]$ ) from admission to immediately pre-MT, at  $24 \pm 12$  hours, and at  $7 \pm 2$  days (or discharge), calculated with 95% confidence intervals.

The analysis of the effect of the group on the mRS at 3 months will be performed by the mixed effects ordinal logistic regression model. It will take into account as explanatory variables the group of intervention, as well as the stratification factors (the site and the baseline NIHSS score [dichotomised 0 to 5 versus 6 or more] as random effects). The effect of the intervention on the occurrence of good collaterals will be assessed by a Wald test and quantified through the adjusted common odds ratio with the associated 95% confidence interval.

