The DOWN-SUITE study will be the first multicenter, randomised, controlled, open-label clinical trial with blinded outcome assessment comparing collateral status in patients with AIS treated with an in-hospital application of HDT15 versus usual positioning before MT. The duration of HDT15 application (approximately 60-90 minutes) is expected to be long enough to detect significant changes in cerebral hemodynamics. Building from preclinical experiments on rodent and non-human primate stroke models carried out by our French-Italian group, it will provide for the first time the translation of HDT15 efficacy on cerebral hemodynamics and clinical outcome from animal models to AIS patients. No therapeutic intervention is currently available to enhance collaterals in AIS.

The DOWN-SUITE trial will provide robust, high-quality evidence on the safety, feasibility and efficacy of HDT15 as a low-cost collateral therapeutic for AIS.

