#### 4.2 Method for randomisation

Central randomisation will be performed by an online, secure, software application (Sealed Envelope; <https://www.sealedenvelope.com>). The group of intervention will be automatically assigned following a pre-established randomisation list completed by the statistician of the study. The allocation ratio between the HDT15 (intervention) and usual position (control) groups will be 1:1. Randomisation will be stratified by site. To take into account the inter-individual heterogeneity in baseline collateral status, randomisation will also be stratified according to score of the National Institute of Health stroke scale (NIHSS) at presentation in the Emergency Room (dichotomised 0 to 5 versus 6 or more), which will be assessed before treatment allocation. Patients with NIHSS 0 to 5 will be considered as having a “minor stroke” despite a M1 occlusion, which will be considered as a surrogate marker of good baseline collaterals.

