## **6 EXPERIMENTAL STRATEGIES**

### **6.1 Study strategy: experimental group**

#### **6.1.1 Description of the strategy**

HDT15 will be applied in the intervention group in 2 different settings:

- in the Emergency Room, by tilting the stretcher to lower the head by -10° to -15° relative to the body of the patient; the degree of tilting will be checked using a dedicated digital inclinometer or a mobile phone app
- in the Angiography Suite, by tilting the angiography table to lower the head by -10° to -15° relative to the body of the patient, depending on the actual technology of the angiography system of each clinical site; the degree of tilting will be automatically checked using the angiography system

HDT15 will start as soon as possible following randomisation in the Emergency Room (i.e. after vascular neuroimaging), and will be maintained during the transfer to the Angiography Suite, as well as during the entire thrombectomy procedure: i.e. HDT15 will end after the completion of MT, when the patient is transferred from the angiography table to her/his bed in a standard flat position.

Application of HDT15 will not delay usual care. The standard in-hospital patient pathway, including transfer from neuroimaging room to the angiography suite and the required procedural steps of MT, will allow sufficient time for the application of HDT15. HDT15 duration is expected to be at least 30 minutes (estimated time 30 to 90 minutes), from start to the assessment of the primary efficacy endpoint.

The actual degree of HDT15 will be between -10° to -15°, depending on the ER stretchers and the angiographic system of each clinical site.

Despite conscious sedation being the preferred approach for MT in participating centers, for patients needing intubation, the HOB will be briefly set to 0° during tube placement to ensure safety, with immediate repositioning to the assigned position (HDT15: -10° to -15°; control: 0° to +30°) post-intubation to maintain protocol adherence.

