## **9 STATISTICAL ASPECTS**

### **9.1 Number of subjects needed**

Considering previous data on distribution of acute stroke patients across the ASITN/SIR collateral scale, a sample size of 118 patients (59 patients per group) should yield 80% power to detect a between group difference of 25% (60% in experimental group versus 35% in control group) for the primary endpoint, which is considered of substantial clinical significance, with a bilateral alpha risk of 0.05.

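### Section 9.3.3 fixes per-arm summaries for the safety outcomes and puncture time, and names no between-arm estimate for these or for percent NIHSS change

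*Protocol*

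**What the plan says.** Section 9.3.3 names an analysis for each secondary outcome.

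- **Binary safety outcomes.** The proportions with vomiting, an NIHSS increase of at least 4 points, SICH and pneumonia "will be calculated with their 95% confidence interval for each group".
- **Blood pressure and oxygen saturation.** A mean with its 95% interval, again by group.
- **Admission-to-puncture time.** It "will be described by median, first and third quartiles (Q1 and Q3) for each group". There is no interval.
- **Percent NIHSS change.** It is listed under efficacy and is to be calculated with 95% confidence intervals. The text does not say whether these are per arm or for a difference.

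Other outcomes are handled differently. Section 9.3.2 gives the primary endpoint a mixed logistic model with an adjusted odds ratio. The end of section 9.3.3 gives the 3-month mRS a mixed ordinal model with a common odds ratio. The mRS is the only secondary outcome with a between-arm analysis.

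Section 3.2 makes delay to puncture and the safety outcomes secondary objectives, to be assessed in both groups. Section 2.1 expects the trial to give "robust, high-quality evidence on the safety, feasibility and efficacy of HDT15", and section 6.1.1 states "Application of HDT15 will not delay usual care".

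**The concern.** Whether tilting causes more vomiting, pneumonia or deterioration, or lengthens the time to puncture, is a question about the difference between randomised arms. Section 9.3.3 fixes a form that describes each arm and stops there. A report that followed it literally would leave the reader with two intervals per safety outcome and, for puncture time, two medians with quartiles and no measure of uncertainty. Setting two 95% intervals side by side is a stricter comparison than a 95% interval for the difference, so a real excess can go unremarked.

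For percent NIHSS change the weakness is an unspecified contrast: an efficacy outcome cannot be judged without one.

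**Working it through.** **Inputs from the protocol.** Section 9.1: "a sample size of 118 patients (59 patients per group) should yield 80% power to detect a between group difference of 25" per cent ("60% in experimental group versus 35% in control group"), "with a bilateral alpha risk of 0.05". Section 4.2: "The allocation ratio between the HDT15 (intervention) and usual position (control) groups will be 1:1".

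**The plan's own figure.** With the unpooled two-proportion formula,

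n = (1.960 + 0.842)² × [0.60×0.40 + 0.35×0.65] / 0.25² = 7.849 × 0.4675 / 0.0625 = 58.7,

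so 59 per arm and 118 in total. The stated size reproduces, and 59 per arm is used below.

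**Assumptions.** The protocol gives no event rates for the safety outcomes, so every count and rate below is illustrative. The safety population in section 9.2 is taken to be 59 per arm.

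**Formulas.** For x events in n, with p = x/n and z = 1.96, the Wilson interval is

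[p + z²/2n ± z√(p(1−p)/n + z²/4n²)] / (1 + z²/n).

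With Wilson limits (l₁, u₁) and (l₂, u₂), the Newcombe interval for p₁ − p₂ runs from

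(p₁ − p₂) − √[(p₁ − l₁)² + (u₂ − p₂)²] to (p₁ − p₂) + √[(u₁ − p₁)² + (p₂ − l₂)²].

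**Example, 12/59 versus 3/59.**
- Arm 1: 20.3% (12.0 to 32.3). Arm 2: 5.1% (1.7 to 13.9). They overlap between 12.0% and 13.9%.
- Difference: 0.2034 − 0.0508 = 0.1525.
- Lower limit: 0.1525 − √(0.0830² + 0.0883²) = 0.1525 − 0.1212 = 0.031.
- Upper limit: 0.1525 + √(0.1193² + 0.0334²) = 0.1525 + 0.1239 = 0.276.
- So 15.3 points, 95% CI 3.1 to 27.6 (Fisher p = 0.024).

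Two further pairs show the same pattern:
- 8/59 versus 1/59: arms 7.0 to 24.5% and 0.3 to 9.0%, which overlap; difference 11.9 points (2.1 to 22.9), Fisher p = 0.032.
- 15/59 versus 6/59: arms 16.1 to 37.8% and 4.7 to 20.5%, which overlap; difference 15.3 points (1.3 to 28.8). This one is borderline, with Fisher p = 0.052.

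**How often the two presentations disagree.** Full enumeration of two independent binomials with 59 per arm:

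| Assumed true rates | Arm intervals separate | Difference interval excludes zero |
|---|---|---|
| 30% vs 10% | 48% | 79% |
| 20% vs 5% | 37% | 71% |
| 10% vs 5% | 2% | 14% |
| 6% vs 3% | 0.5% | 7% |

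**Means (blood pressure, saturation).** With equal SDs, the arm intervals separate only when the means differ by more than 2 × 1.96/√59 = 0.51 SD. A difference interval excludes zero beyond 1.96 × √(2/59) = 0.36 SD. For large samples, requiring separation corresponds to a two-sided level of 2[1 − Φ(1.96√2)] = 0.0056.

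**The case against.** The strongest reply is that this is detail for the statistical analysis plan. Section 9.6 promises such a plan and allows planned analyses to be completed, nothing in 9.3.3 forbids a between-arm estimate, and describing safety by arm is a defensible choice in a proof-of-concept trial powered only for collateral grade. This stands in part: the gap can be closed without contradicting the protocol. It does not remove the point, because 9.3.3 does not leave the form open. It fixes per-arm summaries for these outcomes beside between-arm models for the primary endpoint and the mRS.

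Second, a reader might infer that the plan will treat overlapping intervals as showing no harm. No section says so. Per-arm proportions with denominators, and per-arm means with intervals, also let anyone derive a crude difference. That stands for the safety items. It does not hold for puncture time, where medians and quartiles do not yield an interval for the difference.

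Third, a reader might infer that percent NIHSS change is also restricted to per-arm summaries. The words limiting the analysis to each group are absent there; all that can be said is that no contrast is named.

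Fourth, the examples use fairly high rates. At 10% versus 5% or below, the limit is the sample size and no presentation repairs it. That stands, and the table shows it.

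Finally, the section 2.1 sentence is rationale, and the section 6.1.1 sentence can be read as describing the care pathway. Neither is a formal hypothesis, so the point rests mainly on the objectives in section 3.2.

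**Conclusion.** The point holds as an avoidable weakness of the stated analysis. It is not an error in the primary analysis or the sample size. For blood pressure, saturation, vomiting, NIHSS worsening, SICH, pneumonia and puncture time, the protocol fixes a form that omits the quantity its safety and delay objectives need; for percent NIHSS change it leaves that quantity undefined. The loss is clearest for puncture time, where it cannot be made good from the reported summaries.

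For binary outcomes the gain depends on event rates that the protocol does not give. It is substantial at assumed rates such as 20% versus 5% (71% against 37%) and small in absolute terms at 10% versus 5% (14% against 2%). Even with the difference reported, 59 per arm gives limited precision, so an interval that includes zero would not show absence of harm.

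**What to change.** In section 9.3.3, keep the per-arm summaries and add:

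- for each binary safety outcome, the between-arm risk difference with a 95% interval, for example Newcombe's;
- for blood pressure and saturation, the between-arm mean difference with a 95% interval;
- for admission-to-puncture time, a Hodges-Lehmann shift or difference in medians with a 95% interval;
- for percent NIHSS change, a statement that the 95% interval is for the between-arm difference.

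State that all of these are estimates without significance claims, and that an interval including zero will not be read as absence of harm. The proportion maintaining the tilt is properly a single-arm figure and needs no change.

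The cost is a few lines of text and code. Data collection, sample size and the primary analysis are untouched.

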#### **9.4 Intermediate analyses**

An interim analysis of the primary and secondary outcomes is planned 12 months after the start of recruitment. Based on the results of this analysis and the progress of enrolment, the Steering Committee may consider a reassessment of the sample size and a recalculation of the study's statistical power.

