### 4.3 Endpoints

#### 4.3.1 Primary endpoint

The **primary endpoint** will be the achievement of **good collateral status**, i.e. grade 3 or 4 on the American Society of Interventional and Therapeutic Neuroradiology/Society of Interventional Radiology (ASITN/SIR) collateral scale, in the HDT15 versus control group, as seen at the beginning of MT. The ASITN/SIR collateral grade will be assessed by a blinded central imaging core lab from the pretreatment diagnostic angiographic runs, routinely performed as the first procedural step of MT. Patients achieving complete or partial recanalization (spontaneous or rt-PA-induced) at the first angiographic assessment during MT will be excluded from the primary outcome analysis, since ASITN/SIR score could not be assigned. Details regarding the assessment of the primary endpoint are available in **paragraph 10.2.2.**

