### **7.3.4 Imaging tests required for the project**

Routine neuroimaging (CT or MRI scan at admission, digital subtraction angiography during MT and CT or MRI scan at 24 hours) will be retrieved, anonymised and stored via a dedicated secure platform (XNAT; <https://www.xnat.org>) for the blinded evaluation of imaging

endpoints. This image management will be carried out by the Sponsor under the responsibility of [name].

Imaging data centralisation will be performed continuously during the study. Imaging will be reviewed by the Central Imaging Core Lab by batch in order to obtain all the blinded assessments at the end of the study. Imaging data, produced by the Central Imaging Core Lab, will be stored in the study database. Further details are available in paragraph 10.2.2.

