#### **9.6 Managing changes to the analysis plan**

A detailed statistical analysis plan will be drawn up before the database is frozen. It will take into account any changes in the protocol or unexpected events during the course of the study that have an impact on the analyses presented above. Planned analyses may be completed in line with the study objectives.

Any subsequent changes to the statistical analysis plan must be justified and will result in a new version of the document. These deviations from the analysis plan will be reported in the final report of the study. All documents will be kept in the study file.

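### Section 9.4 lets the Steering Committee re-size the trial on interim results with no rule, cap, firewall or matching final test, so the 5% error rate and the confidentiality of the effect are unprotected

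*Protocol*

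**What the plan says.** Section 9.4 schedules an interim analysis of the primary and secondary outcomes 12 months after recruitment starts. It then says: "Based on the results of this analysis and the progress of enrolment, the Steering Committee may consider a reassessment of the sample size", together with a recalculation of power. It does not say whether the analysis is by arm or pooled, who prepares it, what rule would change the size, or how large the trial may become.

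Section 4.3.1 defines the primary endpoint as good collateral status "in the HDT15 versus control group, as seen at the beginning of MT". Section 9.1 sizes the trial on a single comparison: "a sample size of 118 patients (59 patients per group) should yield 80% power to detect a between group difference of 25" percentage points, "with a bilateral alpha risk of 0.05". Section 9.3.2 tests the primary endpoint with a Wald test and reports an odds ratio with a 95% confidence interval. No other significance level appears.

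Section 8.4 gives the DSMB review of accumulating data and an advisory role to the Steering Committee; 9.4 does not mention it. On the timing of the analysis plan, 9.6 says: "A detailed statistical analysis plan will be drawn up before the database is frozen".

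**The concern.** Two separate things are at stake.

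The first is the type I error. When the final sample size depends on the observed treatment difference and the final test ignores that, the test statistic no longer has its nominal distribution. How far the error moves depends on the rule, and 9.4 has none.

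The second is confidentiality of the effect, which matters whatever the error rate turns out to be. Section 9.4 gives the results to the body that runs an open-label trial. Treating staff cannot be blinded (6.3.1), and under 5.4 the treating physician may discontinue the tilt at discretion. Nothing in 9.4 limits who may learn the trend. Because 9.6 ties the analysis plan only to database freeze, the plan may also be completed after interim results are known.

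**Working it through.** **Inputs from the Protocol.** Rates of 60% and 35%, 118 patients, 80% power, two-sided 0.05 (9.1); 1:1 allocation (4.2); Wald test and 95% interval (9.3.2); interim at month 12 (9.4); 15 months of inclusion (7.1).

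**Assumptions.** Even accrual, so the interim fraction is t = 12/15 = 0.80, about 94 of 118 patients. The final test rejects when |Z| > 1.96. Caps of 1.5, 2 and 3 times the planned size are illustrations, since the Protocol sets none. Normal approximation throughout.

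**Step 1: reproduce the planned size.** With unpooled variances,

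n per arm = (1.960 + 0.842)² × [0.60×0.40 + 0.35×0.65] / 0.25² = 7.849 × 0.4675 / 0.0625 = 58.7,

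so 59 per arm and 118 in total, as stated. This is the size for one test at 0.05, with nothing set aside for an interim.

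**Step 2: error with a data-driven final size.** Let Z1 be the interim statistic, standard normal under the null, and M the final size as a multiple of 118. The final statistic is

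Z = [√t·Z1 + √(M−t)·Z2] / √M, with Z2 an independent standard normal.

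Given Z1 = z, the chance of rejecting is

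A(z, M) = 1 − Φ[(1.96√M − z√t)/√(M−t)] + Φ[(−1.96√M − z√t)/√(M−t)].

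The overall error is A(z, M(z)) averaged over the standard normal distribution of z. If M = 1 whatever z is, this gives 5.0%.

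**Step 3: rules that 9.4 would allow.** Conditional power at the observed effect is

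CP = 1 − Φ[(1.96√M − |z|√t)/√(M−t) − |z|√(M−t)/√t].

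The conditional-power rule takes the smallest M between 1 and the cap with CP ≥ 0.80. The two versions below differ in what is done when no such M exists. The worst-case rows choose, for each z, the M that maximises A.

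| Rule (t = 0.8, final critical value 1.96) | Cap 1.5× | Cap 2× | Cap 3× |
|---|---|---|---|
| Size unchanged, no early claim | 5.0% | 5.0% | 5.0% |
| 80% conditional power; go to the cap if out of reach | 6.1% | 6.6% | 7.2% |
| 80% conditional power; keep 118 if out of reach | 4.8% | 4.7% | 4.7% |
| Worst case, increase only | 6.3% | 7.0% | 7.6% |
| Worst case, reduction or stopping also allowed | 8.5% | 9.1% | 9.8% |

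The second and third rows use the same target and differ only in a detail that 9.4 leaves open, yet one exceeds 5% and the other does not.

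**Step 4: sensitivity to timing.** Slow accrual lowers t. At t = 0.5 the conditional-power rule that goes to a 2× cap gives 6.1%. The increase-only worst case is 5.8%, 6.2% and 6.6% for the three caps.

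**Step 5: what the sections fix about access.** Section 8.4 makes the DSMB the reviewer of accumulating data and the Steering Committee the recipient of its advice. Section 9.4 has the Steering Committee act on the analysis results directly, with no intermediate step. Section 9.6 sets no date for the analysis plan relative to the interim.

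**The case against.** The strongest reply is that much of this is conditional or inferred.

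- **Comparative results are not stated.** Correct: 9.4 does not say by arm. The inference rests on the endpoint being defined as one arm versus the other and on the size being reassessed on the results. It is strong, but it is an inference.
- **The error may not move at all.** Correct. The Committee may only consider a reassessment, and some rules stay below 5%. A reader might infer that the nominal level is already lost; the text does not support that.
- **Two unadjusted looks would give 7.1% at this timing.** That figure requires success to be claimable at month 12. Section 9.4 names no efficacy stop, so it does not describe this plan.
- **The analysis plan may set the method and the final critical value.** It may, and that detail is commonly left there. But the Protocol itself gives the Committee the decision, and 9.6 allows the remedy to be written after the results are seen. The exposure is limited: 9.3.2 already fixes the primary model and sensitivity analyses, and 9.2 places major deviations in a blind review.
- **Core-lab timing.** A reader might see a conflict in 7.3.4, where images are read "by batch in order to obtain all the blinded assessments at the end of the study". Reading in batches does not bar an earlier batch, so this needs a clarifying sentence and is not a contradiction.
- **Knowledge of the trend biasing NIHSS and mRS ratings.** Section 6.3.1 promises blinded assessment of all endpoints, so unblinded rating cannot be assumed. Nor can it be shown that Committee members enrol patients, because the membership pages are not available.
- **The trial is a phase 2a/b proof of concept.** This reduces the cost of a modest inflation, but it does not make releasing the trend harmless.

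**Conclusion.** The point stands as a gap in 9.4. As written, it allows an effect-driven change of sample size with no rule, cap or firewall, followed by a conventional test, and the only level stated is the two-sided 0.05 of 9.1. The error is 5% if nothing changes. It is 6.1–7.2% under a plausible extension rule that goes to the cap when the target is out of reach, at most 6.3–7.6% if the size can only rise, and at most 8.5–9.8% if it can also fall or the trial can stop. These figures assume an interim at 0.8 of the information, a final critical value of 1.96 and caps of 1.5 to 3 times the planned size.

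The confidentiality problem does not depend on those figures: comparative results, once released to the trial's leadership, cannot be recalled. The documents do not show that inflation has occurred, that outcome raters are unblinded, or that the interim reading is impossible.

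**What to change.** **Section 9.4.** State that sample-size reassessment uses arm-blind data only: the pooled good-collateral rate, the pooled rate of exclusion for recanalisation, and accrual. State that there is no efficacy stop and that no comparative efficacy result goes to the Steering Committee. The final test can then stay at 0.05. Any by-arm table goes to the DSMB alone, which returns a recommendation. If an effect-based change is kept, or has already been made, specify a final test that remains valid under it: a combination test with weights fixed in advance, or a conditional-error test.

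**Section 9.6.** Require the analysis plan to be signed before the interim data cut. That date may have passed: 7.1 puts the start in the third quarter of 2024, and the version table lists an amendment after August 2025. In that case, have the plan completed and signed by staff without access to by-arm results, and record this.

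**Section 7.3.4.** Add that a core-lab reading batch precedes the interim.

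**Cost.** Rewording three sections and one earlier reading batch. With the arm-blind option, no patients need be added to pay for the interim. The Steering Committee gives up early sight of the effect.
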